#### Study 1: Pre-post comparison of GEDI MOC in the ED

Study one is a quasi-experiment comparing outcomes for patients seen by the GEDI team to historical controls. As with all quasi-experiments, the disadvantage lies in the internal validity and risk of bias and this experiment will predominantly be affected by selection and historical control bias. Further to the selection bias and given the time difference between the pre and post intervention groups, events within the ED may influence the observed effects and lead to historical bias. Throughout the intervention a record will be made of any process or system changes that occurred within the ED during the GEDI team’s implementation [39]. These will be incorporated into the analysis.

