##### Samples

The study sample comprises frail older persons living in the community or RACF presenting to Nambour General Hospital ED during two time-periods:(i)Time 1: 1^st^ January to 31^st^ December 2012: prior to development of any aspect of GEDI MOC, and(ii)Time 2: GEDI MOC implementation: 1^st^ September 2015 to 31^st^ August 2016

The gap between these two time-periods was when the GEDI MOC was developing, partially staffed and supported and was, therefore, not operating at an optimal level.

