##### Data collection

Data extraction will occur retrospectively via medical records audit of coded state based Health Service databases, namely Emergency Department Information Service (EDIS; Healthcare Group, CSC)® and Hospital Based Corporate Information System (HBCIS; iSoft). SCHHS Health Statistics unit provides linking of the EDIS, HBCIS and financial data providing raw data on all presentations to the ED and those admitted to hospital. The raw data will subsequently be manually cleaned to identify RACF residents based on their home addresses. This is important as RACFs often have independent living community residents at their facilities who needed to be excluded from this cohort. Independent variables that will be used to describe the sample and used to build multivariable models for outcomes are:Demographics - Age, Sex, postcodeDate and time of presentationClinical diagnosis – reason for presentation and ICD-10 code/categorySeen by GEDI team – Yes/NoAustralasian Triage Score [40]Adult Deterioration Detection System Score [41]Next of Kin/Substitute decision maker/Enduring Power of Attorney detailsTime to referral from ED arrivalTime to disposition from ED arrival

Outcome variables collected will be:Disposition - discharged home, moved to short stay area, admitted, diedED LoS – in minutesHospital LoS – in daysAll cause in-hospital mortality within 30 days of ED presentationED Re-presentations in 72 h and 28 daysTime to ED re-presentation within 28 days

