##### Data analysis

Descriptive statistics will be used to describe the intervention and control groups including frequencies, percentages, appropriate measures of central tendency and distribution. We will use survival analysis to jointly model length of stay and disposition, with the four destinations as competing risks. We will use survival analysis for ED representations with out-of-hospital mortality as a competing risk. All models will adjust for the patient level factors of gender, age, triage score, season, day of the week and time of presentation. Pre-post designs are vulnerable to confounding by other changes over time that may be attributed to the intervention [39]. To control for this, we will include a linear trend (based on date) in all models to account for gradual changes that are not captured in the individual variables, e.g., experience of healthcare workforce. We will also adjust for season using a sinusoid with an annual cycle to control for the winter peak in morbidity [42]. The survival analyses will use Cox models and we will check the proportional hazards assumption. The models’ residuals will be checked for outliers and correlation over time. We will calculate Cook’s influential statistic and examine relatively large outliers. We will calculate the variance inflation factor and remove variables with a score above five on the basis that they are co-linear. The key outcome will be the mean effect of the intervention together with 95% confidence intervals. The results will be reported using the Strengthening the Reporting of Observational Studies in Epidemiology (STROBE) guidelines [43].

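### Study 1 gives two different covariate lists for its outcome models, and RACF residence, which the plan goes to some trouble to derive, is on neither

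*Protocol article*

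**What the plan says.** The protocol article describes the covariates for Study 1 in two places.

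- **Study 1, Data analysis:** "All models will adjust for the patient level factors of gender, age, triage score, season, day of the week and time of presentation". A linear date trend and an annual sinusoid are added to these.
- **Study 1, Data collection:** "Independent variables that will be used to describe the sample and used to build multivariable models for outcomes are", followed by a longer list. It includes the reason for presentation with ICD-10 category and the "Adult Deterioration Detection System Score". It also includes an indicator of whether the GEDI team saw the patient, time to referral and time to disposition.

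RACF residence is handled separately in Data collection: "The raw data will subsequently be manually cleaned to identify RACF residents based on their home addresses". The section calls this step important, because independent residents living at the same sites must not be counted as RACF residents. The resulting yes/no variable is then named in neither list.

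The introduction to Study 1 says that "this experiment will predominantly be affected by selection and historical control bias". Under Samples, the control year is 2012, "prior to development of any aspect of GEDI MOC", and the second period is given as "GEDI MOC implementation: 1^st^ September 2015 to 31^st^ August 2016".

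**The concern.** With historical controls, adjustment for case mix is a main defence against attributing a change in patients to a change in care. The reader needs to know which covariates will be used, and the article answers in two ways that do not agree.

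RACF residence matters most because neither answer includes it. The Background says that older patients in general face higher admission rates and longer ED stays, and that this applies particularly to those from RACFs. It also gives RACF patients a high risk of complications and death in hospital, and high rates of re-presentation and re-admission. These correspond closely to the Study 1 outcomes of disposition, length of stay, mortality and re-presentation.

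The two periods start 3 years and 8 months apart, so the share of RACF residents, or the mix of presenting problems, could differ between them for reasons unrelated to GEDI. If so, part of that difference could appear in the estimated effect of GEDI.

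**Working it through.** **1. The lists side by side**

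| Variable | Data collection (model-building list) | Data analysis (all models) |
|---|---|---|
| Age, sex/gender | yes | yes |
| Triage score | yes | yes |
| Date and time of presentation | yes | yes, as season, day of week, time and date trend |
| Reason for presentation / ICD-10 category | yes | not named |
| Deterioration score | yes | not named |
| RACF residence | not named | not named |
| Seen by GEDI, time to referral, time to disposition | yes | not named |

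For presenting problem and deterioration score, the two sections conflict. For RACF residence, there is an omission from both.

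The longer list cannot be adopted whole. Being seen by GEDI is the exposure. Time to referral and time to disposition arise after arrival, and the Study aims name both as outcomes.

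**2. How large could the bias be?** The protocol gives no RACF share, no change in share and no difference in admission risk by residence, so there is no stated figure to reproduce. The following illustration uses a crude difference in admission proportions, which is not the planned Cox analysis.

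Inputs from the protocol:
- Presentations over age 70 per year (Setting): 52,410 × 0.18 = 9,434. This is an upper bound if only frail persons are analysed.
- Admission proportion (Background): about 60%.

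SE of the difference between periods = √(2 × 0.6 × 0.4 / 9,434) = 0.0071, or 0.71 points. The 95% half-width is 1.96 × 0.71 = 1.4 points.

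Bias from an omitted binary factor = change in its share × risk difference between its levels. Both inputs are assumed:

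| Change in RACF share | Risk difference 5 points | 10 points | 20 points |
|---|---|---|---|
| 2 points | 0.10 (0.14 SE) | 0.20 (0.28 SE) | 0.40 (0.56 SE) |
| 5 points | 0.25 (0.35 SE) | 0.50 (0.70 SE) | 1.00 (1.40 SE) |
| 10 points | 0.50 (0.70 SE) | 1.00 (1.40 SE) | 2.00 (2.80 SE) |

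**3. Can the date trend stand in for the missing variable?** Assume even daily volume. Each window has 366 days and the start dates are 1,339 days apart.

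- Between-window variance of date: (1,339/2)² = 448,230.
- Within-window variance: (366² − 1)/12 = 11,163.
- Squared correlation of date with period: 448,230 / 459,393 = 0.976, so r = 0.988.
- Variance inflation factor: 459,393 / 11,163 = 41 (about 48 once the annual sinusoid is included).

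The Data analysis section removes variables with a factor above five, so that rule would flag the trend or the period term itself. If the trend stays, it absorbs a steady linear drift in RACF share. It does not absorb a step between periods. The standard error of the period effect also grows by √41 ≈ 6.4, to about 4.6 points, and the biases in the table then amount to about 0.02 to 0.44 SE. The importance of the omission therefore also depends on what happens to the trend term.

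**The case against.** The strongest reply is that the list in Data analysis is nowhere called exhaustive. It can be read as the core set common to all models, with the Data collection list as the pool from which models are built. On that reading, presenting problem and deterioration score are not left out. This stands in part: a reader might infer that the plan omits all three variables, but the documents do not support that for these two. What remains for them is doubt about which list governs. The reply does not help RACF residence, which is on neither list. Nor is this a detail left to an analysis plan that is not shown, because the article itself states the adjustment set, in two ways.

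A second reply is that age, triage score and the linear trend already give some control, and that recorded process or system changes in the ED are to be incorporated into the analysis. This is also right in part. A reader might infer that any shift in RACF share or presenting problem is credited to GEDI, or that these are the strongest case-mix variables held. The protocol supports neither statement: control is partial rather than absent, and nothing ranks these variables above age and triage score. The crude calculation likewise cannot be turned into a coverage figure for the planned adjusted models.

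A third reply is that RACF share is not purely a confounder. Table 1 gives the GEDI nurses pre-hospital contact with RACFs that bears on transfer decisions, so the service may itself change which residents reach the ED. This stands. It is a reason to show results both ways, not a reason to leave the variable out.

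**Conclusion.** The point holds in a limited form. The two sections disagree on whether presenting problem and deterioration score enter the models. RACF residence is on neither list, although the plan derives it and its own Background ties it to outcomes being measured. In a comparison that the protocol itself says is mainly exposed to selection and historical control bias, a shift in RACF share or presenting problem would be only partly controlled.

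The size of the bias cannot be established from the documents. Under the assumed ranges it goes from 0.14 to 2.8 standard errors of a crude difference, that is, from negligible to larger than the half-width of the interval. It is a smaller fraction of the standard error if the date trend is retained. These figures rest on assumed RACF values, on 9,434 presentations per period and on 60% admission. They show only that the omission cannot be dismissed in advance. The textual conflict and the absence of RACF residence depend on none of these assumptions.

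**What to change.** State one pre-specified set of baseline covariates for all Study 1 models, and make Data collection and Data analysis agree on it:

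- Keep the factors already named for all models.
- Add RACF residence (yes/no).
- Add presenting-problem category as recorded at arrival. Do not use the discharge ICD code, which is assigned after the intervention could have acted.
- Add the first recorded deterioration score, provided that it is available in both periods.
- Do not use the seen-by-GEDI indicator, time to referral or time to disposition as adjustment covariates.
- Report results with and without RACF adjustment, and note that GEDI's contact with RACFs before transfer may alter the RACF share.

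The cost is small, because the variables are already extracted or derived under the plan. The models gain a few parameters, a rule is needed for missing deterioration scores, and each result is shown twice for the RACF comparison.

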## Background

Across the developed and developing world the population is ageing. In Australia it is predicted that, compared to 2005 the proportion of the population over 65 years of age will increase from 13% to 24%, by 2036 [1]. With this increase, the demand on Emergency Department (ED) services by older persons living in the community or in residential aged care facilities (RACF) will increase [1–3]. A systematic review of 27 studies from around the world has demonstrated that the rate of transfer to EDs from RACFs is 0.1–1.5 transfers per RACF bed/year [4].

As a result of this ageing of the population it is imperative that the health care system develop safe models of care (MOC) that span both the community and hospital health care sectors. While the ED is uniquely designed to care for the critically ill or injured, it is often a suboptimal environment for the provision of care to the frail, older person [5, 6]. Prior research shows that older persons who develop an acute illness or who have an acute exacerbation of a chronic condition, have complex medical needs and the doctors and nurses who manage their initial care in the ED often have limited experience in geriatric medicine [7, 8]. Several studies have shown that this situation leads to: under-triage; higher rates of admission; delayed and fragmented care; longer stays in the ED; and unnecessary investigations and invasive interventions [9–19]. For patients from RACFs this is particularly true. During admission to hospital, patients from RACFs are at high risk of complications such as delirium, urosepsis, falls and death [20–22]. Patients from RACFs who develop an acute illness or an exacerbation of a chronic condition also suffer high rates of re-presentation to the ED and subsequent re-admission to hospital [2, 10, 12, 14].

Several studies indicate that a large percentage of frail older persons living in the community or RACFs express a preference for treatment in their home if appropriate [23, 24]. Despite this, approximately 60% of ED presentations lead to hospital admission [25, 26]. In an attempt to keep frail older persons at their place of residence during an acute illness, several MOC have been designed and tested. Broadly, the different MOC are divided into those that: i) provide in-home care or outreach of services from one service to another [12, 24, 27, 28]; ii) provide prioritisation or geriatric focused care in the ED [29–32]; or iii) support or enhance primary care [28, 33].

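### Apart from a linear date trend that the plan's own collinearity rule would probably remove, nothing in the Study 1 models separates a change in ED demand from a GEDI effect on ED length of stay

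*Protocol article*

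**What the plan says.** Under Study 1, Data analysis, the protocol article fixes the adjustment set: "All models will adjust for the patient level factors of gender, age, triage score, season, day of the week and time of presentation". It recognises that a before/after comparison is open to confounding by other changes over time, and its stated control is that "we will include a linear trend (based on date) in all models to account for gradual changes that are not captured in the individual variables". For season it adds: "We will also adjust for season using a sinusoid with an annual cycle". The same paragraph sets a collinearity rule: "We will calculate the variance inflation factor and remove variables with a score above five on the basis that they are co-linear".

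The Study 1 introduction warns that "events within the ED may influence the observed effects and lead to historical bias". It says that process and system changes in the ED will be recorded during the intervention and used in the analysis, without saying how.

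Under Study 1, Data collection, the candidate variables are all at patient or presentation level. The linked extract, however, is described as "providing raw data on all presentations to the ED and those admitted to hospital", and date and time of presentation are among its variables. ED length of stay in minutes is an outcome.

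Under Samples, the periods are calendar year 2012 and September 2015 to August 2016.

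**The concern.** How long a patient stays in an ED plausibly depends on how many others arrive that day. If arrivals differed between the two years, length of stay would differ for everyone, with or without GEDI. The article itself expects that "the demand on Emergency Department (ED) services by older persons living in the community or in residential aged care facilities (RACF) will increase". A rise in load would hide a GEDI benefit and a fall would imitate one. The models contain no measure of load, so the date trend is the only term that could take up such a change. Whether that term survives and does its job is the question.

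**Working it through.** The article gives no figure to reproduce here. I took the intervention term to be a before/after indicator, in line with the first study aim, and used least squares on log ED length of stay as a stand-in for the Cox model.

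**Inputs from the article.** Period 1 has 366 days (2012). Period 2 has 366 days (1 September 2015 to 31 August 2016). The gap is 973 days, so the starts are 366 + 973 = 1,339 days (3.67 years) apart. The ED sees 52,410 presentations a year, 18% of them over 70: 9,434 older and 42,976 other presentations, or 42,976 / 366 = 117.4 others a day.

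**Step 1: collinearity of trend and period.** With equal windows of L = 366 days and starts D = 1,339 days apart:
- within-window variance of date = (L² − 1)/12 = 11,163
- between-window variance = (D/2)² = 448,230
- VIF = (448,230 + 11,163)/11,163 = 41.2

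With the annual sinusoid and day of week added, the VIF is 48.2 for period and 48.4 for date. Both are far above five. Period is the quantity of interest, so the trend is the term likely to go.

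**Step 2: where a demand change ends up.** Assume a 10% change in demand and an elasticity of length of stay to demand of 0.25, 0.5 or 1.0. Spurious period effect on log length of stay:

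| Shape of the change | Trend kept | Trend dropped |
|---|---|---|
| Linear in date | 0 / 0 / 0 | 0.025 / 0.05 / 0.10 |
| Half linear, half step in the gap | 0.0125 / 0.025 / 0.05 | 0.025 / 0.05 / 0.10 |
| Step in the gap | 0.025 / 0.05 / 0.10 | 0.025 / 0.05 / 0.10 |

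**Step 3: price of keeping the trend.** With 9,434 patients per period and an assumed SD of log length of stay of 0.7, the 95% half-width is 1.96 × 0.7 × √(2/9,434) = 0.020 without the trend. With it, the half-width is 0.020 × √48.2 = 0.139, about seven times wider.

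**Step 4: illustrative size without the trend.** Demand ratio = (1 + g)^3.67, which is 1.075, 1.114 and 1.155 for assumed g of 2%, 3% and 4% a year. Bias = ratio^elasticity − 1:
- 2% growth: 2.2% to 7.5% for elasticity 0.3 to 1.0
- 3% growth: 3.3% to 11.4%
- 4% growth: 4.4% to 15.5%

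The low end, about 0.022 on the log scale, is as large as the half-width of 0.020 in Step 3.

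**Step 5: would an under-70 arrivals term help?**
- *Collinearity.* Growth of 2–4% a year adds 8.9 to 18.2 arrivals a day. The daily SD is 10.8 if Poisson (√117.4), or 14.1 if 30% larger. VIF against period = 1 + (increase/2)²/SD², from 1 + 4.45²/14.1² = 1.10 to 1 + 9.1²/10.8² = 1.7. The term survives the rule.
- *Bias if capacity was fixed.* In a simulation with a 10% step, 10% daily noise in demand and elasticity 0.5, the spurious effect was 0.050 unadjusted, 0.046 with the trend (standard error 0.077), and about 0.000 with the load term in place of the trend (standard error 0.011).
- *Bias if capacity grew with demand.* The true between-period shift from demand is then 0. The load coefficient, learned from day-to-day variation, still subtracts 0.5 × 0.10 = 0.05, so a spurious shortening of 0.05 appears in GEDI's favour.

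**The case against.** The strongest reply is that the plan already handles this. It recognises confounding over time and puts a linear trend in every model. Steady compound growth with a constant elasticity is exactly linear on the log scale, so with the trend kept the 2–15% range falls to about zero. Collinearity by itself costs precision and does not create bias. This stands, and it limits the point: the bias needs either the VIF rule to remove the trend or a demand change that was not linear in date.

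The record of process and system changes is a second safeguard. It counts for less: it does not clearly cover arrival volume, is kept only during the intervention and so cannot describe 2012, and has no stated method of use.

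Three further objections stand in part. The article's remark on rising demand concerns older persons, whom an under-70 count leaves out. A load coefficient estimated from daily variation reflects short-run surges at fixed capacity and may not carry over to a difference across 3.67 years. The extract is described as covering all presentations, but within a section about an older-person sample, so its scope should be confirmed.

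It can also be said that one extra covariate is a detail for the analysis plan. But the article fixes the adjustment set for all models and also fixes the rule that would undo its only control for time.

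**Conclusion.** The point holds in a conditional form. The models contain no measure of ED load, and the one term that could absorb a change in demand has a VIF of about 48 under a rule that removes anything above five. If the trend goes, the whole demand change falls on the GEDI estimate for ED length of stay. If it stays, only a step or non-linear change does, with an interval about seven times wider.

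A reader might infer that a demand change will be read as a GEDI effect, or that a bias of 2% to 15% is to be expected. The documents support neither. They give one annual volume and no separate figures for the two years, so whether demand changed, by how much and in which direction is unknown. The 2–15% range rests on assumed growth and elasticity and applies only to a model without the trend.

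The collinearity figures rest on the stated dates, equal weight per day and a before/after intervention term.

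**What to change.** Pre-specify a sensitivity analysis for the ED length of stay and disposition models:

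- Derive from the extract the number of arrivals aged under 70 on the day of presentation, or in the preceding hours, after confirming that the extract covers all ages in both periods.
- Add it as a smooth or log-linear term, and report the GEDI effect with and without it.
- Report under-70 volumes for both periods, so that the reader can see whether demand moved.
- Avoid occupancy and older-patient counts as the load measure, because GEDI may change them.
- State in advance whether the date trend is exempt from the VIF rule.

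The plan should state the downside. The load coefficient is a short-run effect at fixed capacity; it over-adjusts, and can imitate a GEDI benefit, if staffing or beds grew with demand. It also leaves out older-patient demand. The estimate with the term fits the case of no capacity change and the one without it the case of full capacity change, so the two should be read as a bracket.

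The cost is one derived variable and one more model term, from data that the article says are already supplied.
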